## Abstract

**Background:**

According to the International Association for the Study of Pain (IASP), the term temporomandibular disorder (TMD) regards a subgroup of orofacial pain, the symptoms of which include pain or discomfort in the temporomandibular joint, ears, masticatory muscles and neck on one or both sides, as well as joint sounds, limited mandibular movements or mandibular deviation and difficulties chewing. Phototherapy, such as low-level laser therapy (LLLT) and light-emitting diode (LED) therapy, is one of the resources used to treatment muscle pain. Thus, there is a need to investigate therapeutic resources that combine different wavelengths as well as different light sources (LLLT and LED) in the same apparatus.

The aim of the proposed study is to evaluate the effects of four different doses of phototherapy on pain, activity of the masticatory muscles (masseter and bilateral anterior temporal) and joint mobility in individuals with temporomandibular disorder. A further aim is to determine the cumulative effect 24 and 48 hours after a single session.

**Methods/Design:**

A placebo-controlled, double-blind, randomized, clinical trial will be carried out involving 72 women between 18 and 40 years of age with a diagnosis of myogenous TMD. The participants will then be randomly allocated to four groups totaling 18 individuals per group. Three groups will be submitted to a single session of phototherapy with different light sources, and one group will receive placebo therapy: Group A (2.62 Joules); Group B (5.24 Joules); Group C (7.86 Joules); and Group D (0 Joules). The following assessment tools will be administered on four separate occasions (baseline and immediately after, 24 h after and 48 h after phototherapy). Pain intensity will be assessed using the visual analog scale for pain, while pain thresholds will be determined using algometer, and electromyographic (EMG) analysis on the masseter and anterior temporal muscles.

**Discussion:**

The study will contribute to the practice of the evidence-based use of phototherapy in individuals with a myogenous TMD. Data will be published after the study is completed.

**Trial registration:**

This study is registered with the Brazilian Registry of Clinical Trials, NCT02018770, date of registration: 7 December 2013.

## Background

According to the International Association for the Study of Pain (IASP) [1], the term temporomandibular disorder (TMD) regards a subgroup of orofacial pain, the symptoms of which include pain or discomfort in the temporomandibular joint, ears, masticatory muscles and neck on one or both sides, as well as joint sounds, limited mandibular movements or mandibular deviation and difficulties chewing. Muscle pain is one of the most common and limiting clinical manifestations of this condition [2–5]. The main causes of TMD are trauma involving local tissues, chronic repetitive microtrauma, non-habitual use of the mandible and an increase in emotional stress [6]. With regard to prevalence, it is estimated that 20% of the population worldwide have TMD, but only 10 to 20% of affected individuals seek some form of treatment [7, 8]. Phototherapy, such as low-level laser therapy (LLLT) and light-emitting diode (LED) therapy, is one of the resources used by dentists and physiotherapists to treat TMD. Due to the low energy intensity and wavelengths capable of penetrating biological tissues, LLLT is believed to influence the synthesis, release and metabolism of numerous signaling substances involved in analgesia [9, 10]. This resource is reported to lead to an increase in the level of beta-endorphins, a reduction in bradykinin, a reduction in the release of histamine, an increase in lymphatic flow, reductions in swelling and pain-related substances, an increase in blood supply, a reduction in the duration of inflammation and the induction of muscle relaxation [11, 12]. LED therapy has been used for the same purposes and has demonstrated similar results, while offering the advantages of a lower cost and greater equipment durability [13, 14]. However, an exhaustive review of the literature has revealed no studies involving the use of phototherapy with different light sources (LLLT and LED) on the same device for application to the masseter and temporal muscles in individuals with myogenous TMD. Knowledge regarding the clinical effects of these forms of phototherapy can contribute to the indication of the best therapeutic resource for such patients. the use of therapeutic appliances that combine different sources of light may be advantageous, especially as devices with this feature began to be available in recent years commercially, making it necessary to research primarily on effects and the choice of best parameters, primarily analyzing immediate effect to later assess cumulative dose effects on the masticatory muscles in patients with TMD.

The aim of the proposed study is to evaluate the effects of four different doses of phototherapy (0, 2.62, 5.24 and 7.86 Joules) on pain, activity of the masticatory muscles (massester and bilateral anterior temporal) and joint mobility in individuals with temporomandibular disorder (TMD). A further aim is to determine the cumulative effect 24 and 48 hours after a single session. The hypothesis is that individuals with TMD submitted to phototherapy with different light sources (LLLT and LED) contained in a single device with a dose of 7.86 will experience a greater reduction in pain and change in electromyographic activity of the masticatory muscles in comparison to individuals submitted to lower doses and the effects of a single session of phototherapy will be maintained for 24 and 48 hours.

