#### Final evaluations

Immediately after, 24 hours after and 48 hours after the end of the treatment phase, the final evaluations will be performed, following the same sequence used in the initial evaluation (Figure 1).

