### Sample size

The sample size was calculated considering α = 0.05 (5% chance of a type I error), 1-β = 0.95 (% of sample power) and data from a visual analog scale (VAS) reported in the study by Pereira *et al*. [21]. The minimum number for each group was determined to be 15 individuals, to which 20% was added to compensate for possible dropouts during the study (total: 18 individuals per group). This calculation was performed using the G*Power software program [22]. Seventy-two individuals will be allocated to different groups (18 individuals per group) through a randomization process involving opaque envelopes containing cards stipulating one of the three following groups: A (2.62 Joules), B (5.24 Joules), C (7.86 Joules) and D (0 Joules).

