### Data analysis

Pain will be the primary outcome and will be determined using a VAS and algometer. EMG will be the secondary outcome. The independent variables will be the different light sources used for phototherapy. The dependent variables will be derived from the pre-treatment and post-treatment evaluations. Intra-group comparisons will be performed using repeated-measures analysis of variance (ANOVA or Friedman’s test), followed by either the Student’s t-test or Wilcoxon’s test. Inter-group comparisons will be performed using either one-way ANOVA or the Kruskal-Wallis test. The choice of tests will be determined by the distribution (normal or non-normal) of the data. The level of significance will be set to 5% (*P* <0.05). All comparisons and statistical analyses will be performed using the SPSS program, version 13.0 (Chicago, IL, USA). Cohen’s d will be employed to determine the clinical effect size of the proposed therapies, with the interpretation of the coefficients based on the classification established by Cohen [23]: 0.2 = small effect; ≥0.5 = moderate effect; ≥0.8 = large effect.

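### The hypothesis that effects last to 24 h and 48 h is paired only with difference tests, which at 15–18 per arm cannot reliably separate full from half retention and give no placebo-adjusted estimate of loss

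*Protocol article*

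**What the plan says.** The Background section sets a secondary question: "A further aim is to determine the cumulative effect 24 and 48 hours after a single session". The hypothesis in the same section then says that "the effects of a single session of phototherapy will be maintained for 24 and 48 hours". Under Final evaluations the visits that serve it are fixed: "Immediately after, 24 hours after and 48 hours after the end of the treatment phase, the final evaluations will be performed".

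The Data analysis section gives the tests. Within arms: "Intra-group comparisons will be performed using repeated-measures analysis of variance (ANOVA or Friedman’s test), followed by either the Student’s t-test or Wilcoxon’s test". Between arms it names one-way ANOVA or Kruskal-Wallis. The significance level is 5%, and Cohen's d is added as a descriptive effect size. The section names neither a contrast of each dose with placebo nor an interval for the loss between visits, and it does not define *maintained*.

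On numbers, the Sample size section says "The minimum number for each group was determined to be 15 individuals", at α = 0.05 and power 0.95 from the VAS data of a cited study, raised by 20% to 18 per arm. It mentions no durability target.

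**The concern.** A claim that an effect is maintained can mean that it is still present, or that it has not been materially lost. The named tests are not matched to either meaning.

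- **Immediate versus 24 h or 48 h, within an arm.** If this is non-significant, a reader may conclude that nothing was lost. That treats lack of evidence as evidence, and it favours small or noisy arms.
- **Baseline versus 24 h or 48 h, within an arm.** If this is significant, pain is still below baseline. The fall includes any placebo response. Because entry requires a VAS above 3, it may also include regression to the mean. It does not show how much of the immediate effect was kept.
- **Overall test across the four arms at 24 h or 48 h.** This uses the placebo arm and bears on whether any effect is still present. An omnibus P value, however, does not say which dose differs from placebo, by how much, or what was lost since the immediate reading.

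At stake is what the trial may conclude about the duration of effect, which is the purpose of the two late visits.

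**Working it through.** **Inputs from the article.** n = 15 per arm before and 18 after the dropout allowance; α = 0.05, taken here as two-sided because the article does not say; power 0.95. No mean difference, SD or between-visit correlation is given.

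**The plan's own figure.** 15 × 1.2 = 18 and 4 × 18 = 72, as stated. The 15 itself cannot be recomputed without the effect size and test. Solving backwards for n = 15 at power 0.95 gives a standardised difference of 1.36 for a two-sample t-test, 1.00 SD of the change for a paired t-test, or f = 0.55 for a four-group one-way ANOVA.

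**Step 1: a loss of 0.5 SD of the within-person change.** For a paired t-test the noncentrality is λ = d_z√n. The miss rate is the probability that a noncentral t with n − 1 df stays within ±t(0.975, n − 1).

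- n = 15: λ = 0.5 × 3.873 = 1.94, critical value 2.145, miss rate 56%.
- n = 18: λ = 0.5 × 4.243 = 2.12, critical value 2.110, miss rate 48%.

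If the sample size came from the paired calculation (d_z = 1.00), 0.5 is exactly half of the planned effect.

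**Step 2: dependence on effect size and correlation.** Let E be the immediate effect in cross-sectional SDs and r the correlation between visits (both assumed), with equal SDs at all visits. A half loss then has d_z = 0.5E / √(2(1 − r)). The chance that this half loss is non-significant, n = 15 / n = 18, is:

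| E | r = 0.3 | r = 0.5 | r = 0.7 | r = 0.8 |
|---|---|---|---|---|
| 0.5 | 88% / 86% | 85% / 83% | 79% / 75% | 70% / 65% |
| 0.8 | 77% / 73% | 70% / 64% | 54% / 46% | 37% / 28% |
| 1.0 | 67% / 61% | 56% / 48% | 36% / 27% | 19% / 12% |
| 1.36 | 46% / 37% | 31% / 22% | 12% / 6% | 3% / 1% |

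At E = 1.0 and r = 0.9 the rates are 2% / 1%.

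**Step 3: the within-arm comparison with baseline.** When half the effect is lost, the distance from baseline to the late visit equals the distance from the immediate to the late visit. With equal SDs and correlations the two tests have the same power. So the chance that the late visit still differs from baseline is one minus the table entry. At E = 1.36 and n = 18 this is 78% for r = 0.5 and 94% for r = 0.7. Where a non-significant loss is rare, a significant difference from baseline is common, so the two within-arm tests do not protect each other against calling a half-lost effect *maintained* in the no-loss sense.

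**Step 4: precision of a placebo-adjusted loss.** For the change from the immediate to a late visit, active minus placebo, the 95% CI half-width in cross-sectional SDs is t(0.975, 2n − 2) × √(2(1 − r)) × √(2/n).

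- n = 18: r = 0.5 gives 2.032 × 1.000 × 0.333 = 0.68; r = 0.7 gives 2.032 × 0.775 × 0.333 = 0.52.
- n = 15: r = 0.5 gives 0.75; r = 0.7 gives 0.58.

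For E = 1.0 a half loss is 0.5 SD. Even an observed loss of zero would therefore not exclude a half loss in these cases. A formal test with a known margin of 0.5 SD and no true loss would have 31% power at n = 18 with r = 0.5, and 47% with r = 0.7. Reaching 80% would take about 64 and 39 per arm.

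**The case against.** The strongest reply is that *maintained* may simply mean still present at 24 h and 48 h. Difference tests suit that meaning, and the planned between-arm comparison, with a 0 J arm and both late visits, can address it. This stands: the hypothesis cannot be treated as a no-loss claim by definition, and the within-arm tests are not the only route. On this meaning the high pass rates in step 3 are partly just power to detect a real remaining effect. What does not fall away is that the overall between-arm test, as named, gives neither the size of each dose's remaining effect versus placebo nor the loss.

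A reader might infer that the plan will report a faded effect as maintained whenever the immediate-versus-late test is non-significant. The documents do not support this: nowhere do they say that non-significance will be read that way.

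Nor can it be said without conditions that a half loss would often be missed. At E = 1.36 and r of 0.7 or more the miss rate is 12% or less.

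It is also fair that durability is a further aim, that the sample size text does not address it, and that an article may leave a margin or decision rule to a fuller document. The point therefore rests on the mismatch between a stated hypothesis and the stated tests, and not on an absent margin.

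**Conclusion.** The concern holds in a limited form. The hypothesis about 24 h and 48 h is stated, and so are the tests; as named, those tests neither estimate nor bound the loss of effect net of placebo. With 15 to 18 per arm, within-arm difference tests cannot reliably tell full from half retention unless the effect is very large or the visits are highly correlated. A loss of 0.5 SD of the within-person change is missed 48–56% of the time. For effects up to 1.0 SD and correlations up to 0.7, a half loss is missed 27–88% of the time; for 1.36 SD and correlations of 0.3 to 0.5, 22–46%.

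These figures assume a two-sided paired t-test, equal SDs and correlations across visits, and values of E and r that the article does not supply. The point matters for the wording of the durability conclusion. It does not touch the comparison of doses immediately after treatment.

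**What to change.** In Data analysis, for each active dose:

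1. Report the VAS difference from placebo in change from baseline at 24 h and at 48 h, with 95% CI, as the test of whether an effect is still present.
2. Report the placebo-adjusted VAS change from the immediate reading to 24 h and to 48 h, with 95% CI, as the estimate of loss.
3. State that a non-significant within-arm test will not be read as maintenance.
4. Word the conclusion as an effect versus placebo still present at 24 h or 48 h, unless the interval for loss supports more.

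Do not add a formal margin of half the observed effect. That effect is unknown in advance, so the margin could not be fixed beforehand, and step 4 of the working shows that such a test would be badly underpowered here.

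The cost is a few sentences and 3 doses × 2 visits × 2 contrasts = 12 estimates from data already planned. No patients or visits are added. Recruitment is under way, and the statistician stays blinded until the analyses end, so the wording can be settled before the allocation is opened. The real downside is that the interval for loss will be wide at this sample size, so the durability conclusion may be weaker than the hypothesis.

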## Methods/Design

### Overview of research design

A double-blind, placebo-controlled, randomized, clinical trial is proposed to compare the effects of different doses of phototherapy in individuals with myogenous TMD. After screening, individuals with myogenous TMD (based on the Research Diagnostic Criteria for Temporomandibular Disorders (RDC/TMD) will be selected. The following evaluations and assessment tools will be administered: visual analog scale (VAS), algometry for pain, and electromyographic (EMG) analysis. Seventy-two individuals will be allocated to different groups (18 individuals per group) through a randomization process involving opaque envelopes containing cards stipulating one of the three following groups: A (2.62 Joules), B (5.24 Joules), C (7.86 Joules) and D (0 Joules). The study will be divided into three evaluation phases and a treatment phase:

#### Initial evaluation

The individuals who meet the eligibility criteria will undergo an initial evaluation in the following sequence: VAS, algometry for pain and EMG analysis on the masseter and anterior temporal muscles.

#### Treatment phase

Following randomization, the phototherapy will be carried out on the masseter and temporal muscles that are presenting pain.

#### Final evaluations

Immediately after, 24 hours after and 48 hours after the end of the treatment phase, the final evaluations will be performed, following the same sequence used in the initial evaluation (Figure 1).

**Figure 1 Fig1:**
[figure not shown]
**Flow chart of experimental design.**

### Blinding

The participants will be blinded to the allocation. A researcher will be responsible for the randomization process and programming of the phototherapy device based on the results of the randomization. A second researcher will perform the phototherapy and will be blinded to the doses and allocation of the participants. These researchers will not participate in the evaluations, which will be performed by a third researcher blinded to the allocation of the participants. The statistician will also be blinded to the allocation of the participants until the end of the statistical analyses.

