**Table 2 Tab2:** **Phototherapy parameters**

Number of super-pulsed lasers	1 Super-pulsed laser
Wavelength (nm)	905
Frequency (Hz)	1000
Average optical output (mW)	0.9
Peak power (W)	8.5
Dose (J) total per group (20s, 40s, 60s)	0.018; 0.036; 0.054
Spot size (cm2)	0.4
Number of red LEDs	4 Red
Wavelength (nm)	640(±10 nm)
Frequency (Hz)	2
Average optical output (mW)-each	15
Dose (J) each emitter per group (20s, 40s, 60s)	0.3; 0.6; 0.9
Dose (J) total per group (20s, 40s, 60s)	1.2; 2.4; 3.6
Spot size (cm2)-each	0.9
Number of infrared LEDs	4 infrared
Wavelength (nm)	875(±10 nm)
Frequency (Hz)	16
Average optical output (mW)-each	17.5
Dose (J) each emitter per group (20s, 40s, 60s)	0.35; 0.70; 1.05
Dose (J) total per group (20s, 40s, 60s)	1.4; 2.8; 4.2
Spot size (cm2)-each	
Magnetic field (mT)	35
Treatment time (s)	20; 40 or 60
Aperture of device (cm^2^)	4
Total delivered energy (J) per point	2.62; 5.24 or 7.86
Total delivered energy (J) per individual	26.20; 52.40 or 78.60

For the blinding of the participants, the phototherapy equipment with the different light sources has two identical application hand pieces provided by the manufacturer - one with an active tip and the other for placebo applications (does not emit energy), but both with the same sound device. The tips will be denominated X and Y by a researcher who will not participate in the application or evaluations. The researchers who will administer the phototherapy procedures and those in charge of the evaluations will be blinded to which hand piece has the active effect and which is for the placebo application. The hand pieces will only be identified at the end of the data collection process. Table 2 displays the doses and application times for each group.

Phototherapy with the different light sources will be applied to two points of the masseter muscle bilaterally and three points on the temporal muscle bilaterally (totaling 10 application points), based on the results of the clinical exam performed using the RDC/TMD. The same points will be evaluated using an algometer.

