Phototherapy will be applied by one of the researchers in an isolated room with only the researcher and the volunteer present. The researcher will receive the pre-programmed hand piece. Both the researcher and volunteer will be wearing eye protection equipment. The volunteer will be in the supine position on a cot with lower limbs supported on a roll of foam rubber measuring 20 cm in diameter and head supported on a pillow to provide a comfortable resting posture. Phototherapy will be applied using the point technique in contact with the skin with a beam area of 4 cm^2^ (device aperture). The placebo group will be submitted to the same procedures as the groups submitted to phototherapy. Only the coordinator will have knowledge regarding the different phototherapy and placebo applications. At the end of the study, the individuals in the placebo group will be submitted to treatment with active phototherapy.

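### Dose is set only by how long the hand piece is held, so the operator cannot be blind to dose as stated, and contact time is confounded with dose across the active arms

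*Protocol article*

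**What the plan says.** The Blinding section of the protocol article assigns three roles. One researcher randomises and programs the device. Another delivers treatment: "A second researcher will perform the phototherapy and will be blinded to the doses and allocation of the participants". A third, also blinded, does the evaluations.

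The Phototherapy section describes how this is achieved. There are two identical hand pieces with the same sound, one of which does not emit: "The tips will be denominated X and Y by a researcher who will not participate in the application or evaluations". The operator receives a pre-programmed hand piece and applies it in skin contact at 10 points, alone with the participant. On placebo, the section says: "The placebo group will be submitted to the same procedures as the groups submitted to phototherapy".

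The same section also states: "Table 2 displays the doses and application times for each group". Table 2 lists treatment times of 20, 40 or 60 s against energies per point of "2.62; 5.24 or 7.86" joules. It gives one value of average output for each type of emitter and no treatment time for the 0 J group.

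The last paragraph of the Background gives the hypothesis that 7.86 J reduces pain more than the lower doses. The Data analysis section makes pain, measured by VAS and algometer, the primary outcome.

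**The concern.** If output is fixed and only time varies, the person holding the hand piece is told the dose by the clock. Programming by someone else hides the setting but not the elapsed time. Identical hand pieces with the same sound hide whether energy is emitted, but not for how long the tip is applied.

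Two things are at stake. First, the article claims a level of blinding that the procedure does not deliver, and readers of the results would rely on it. Second, the dose comparison is also a comparison of session length. Both parts of the primary outcome depend on the participant's own response: a mark on a line for the VAS, a raised hand for the algometer. A blinded evaluator does not remove an effect that the participant carries out of the treatment room. The participant has experienced the duration, with only an operator who can infer the dose.

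**Working it through.** **Inputs (Table 2 and the Phototherapy section).**
- Laser: 1 diode at 0.9 mW
- Red LEDs: 4 at 15 mW each
- Infrared LEDs: 4 at 17.5 mW each
- Time per point: 20, 40 or 60 s
- Application points: 10

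**Step 1: reproduce the plan's energies.** Total output = 0.9 + 4 × 15 + 4 × 17.5 = 130.9 mW. Energy per point = 0.1309 W × time.

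| Time per point | Computed energy per point | Stated | Computed energy over 10 points | Stated | Contact time over 10 points |
|---|---|---|---|---|---|
| 20 s | 2.618 J | 2.62 J | 26.18 J | 26.20 J | 200 s |
| 40 s | 5.236 J | 5.24 J | 52.36 J | 52.40 J | 400 s |
| 60 s | 7.854 J | 7.86 J | 78.54 J | 78.60 J | 600 s |

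The stated figures are reproduced to rounding (7.86 is 3 × 2.62). No other parameter in the table differs between active arms, so time alone explains the dose.

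**Step 2: dose against contact time.** Energy is a constant multiple of time, so the correlation between them across the three active arms is 1.0. The range is threefold, from 200 s to 600 s. No analysis of these arms can separate an effect of energy from an effect of time in contact.

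**Step 3: placebo.** The article gives no placebo duration, so each possibility is an assumption. The entries are active minus placebo time per point.

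| Placebo duration assumed | Group A (20 s) | Group B (40 s) | Group C (60 s) |
|---|---|---|---|
| 20 s for all | 0 | +20 s | +40 s |
| 40 s for all | −20 s | 0 | +20 s |
| 60 s for all | −40 s | −20 s | 0 |

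Any single duration is matched to one active arm only. If the 18 placebo participants were split 6/6/6, their mean time would be 40 s and each active arm would have 6 duration-matched controls. With a common standard deviation SD, the standard error of an 18 versus 6 comparison is SD × √(1/18 + 1/6) = 0.471 SD. For 18 versus 18 it is SD × √(1/18 + 1/18) = 0.333 SD. The matched comparison therefore has a standard error √2 = 1.41 times as large.

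**Step 4: set the sections side by side.** The Blinding section says the operator does not know the dose. The Phototherapy section has that operator apply the tip by hand, and Table 2 makes application time the dose. Nothing in the article says that contact time is equalised.

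**The case against.** The strongest reply is that varying energy through time at fixed output is a legitimate design choice, and that the blinding that matters most may survive. Seeing 20, 40 or 60 s does not by itself reveal whether the tip emits; the hand-piece code protects that. The operator takes no part in evaluation, each participant has one session in one arm, and nothing suggests that participants can compare durations. Much of each visit (EMG readings, algometry with rest intervals) is common to all arms. The documents give no evidence that up to 400 s of extra contact relieves pain. All of this stands. It limits the likely size of any bias, but it does not make the dose-blinding statement true or separate time from dose.

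A reader might infer more than the text supports:
- **That placebo has one fixed duration, so only one active–placebo comparison is time-matched.** No duration is given, and the wording is compatible with a mix of all three. The defect is that the duration is undefined.
- **That sound is the only feature matched.** The hand pieces are described as identical as well as sound-matched.
- **That the red LEDs give the active tip away.** The tip is in skin contact and both people wear eye protection; whether light can be seen is not stated.
- **That the fixed X and Y labels mean one slip unblinds everyone.** The evaluator and statistician do not handle the tips. Guessing from unequal use (54 active, 18 placebo) is possible but conjectural.

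**Conclusion.** The concern holds in a limited form. As described, the operator is not blind to dose among the active arms. This follows from the article's own Table 2, whose energies are reproduced to rounding from output and time alone. Contact time (200, 400 and 600 s) is completely confounded with dose in the comparison that the hypothesis addresses, whatever is done with placebo. The placebo duration is undefined.

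The direction and size of any resulting bias are unknown. The conclusion rests on two assumptions: that an operator can tell a 20 s hold from a 60 s hold repeated at 10 points, and that apparent contact time is not equalised by some step the article omits. Blinding of participant, operator and evaluator to active versus placebo is not shown to fail.

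**What to change.** Reconcile the Blinding section, the Phototherapy section and Table 2, and state the application time used for placebo.

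**Preferred, where the device allows.** Make apparent application time, meaning both contact and sound, the same in all four arms, with each arm's emitted energy unchanged. Do this without any arm-specific change of tip, because a swap partway through would itself be a cue. The cost is device programming and up to 600 − 200 = 400 s more per session in the shortest arm. The documents do not say whether sound can continue after emission ends, or whether longer contact would alter exposure to the 35 mT magnetic field listed in Table 2. Both need checking first.

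**Otherwise:**
- Balance the placebo participants over the three durations, 6 each, accepting that duration-matched comparisons are imprecise.
- Withdraw the statement that the operator is blinded to dose, and claim only blinding to active versus placebo.
- Limit the dose-response conclusion, stating that dose and contact time cannot be separated.

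This costs an addition to the allocation scheme and some text. Participant-specific hand-piece codes in place of the fixed X and Y labels are an optional, inexpensive safeguard. The Trial status section reports that recruitment is under way, so the change should be made promptly; confounding by design cannot be removed at analysis.
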